### Statistical approach

Continuous variables will be presented as the mean ± standard deviation (SD), median or interquartile range (IQR), and as frequencies or percentages for categorical variables. The comparability of the characteristics between the two groups will be assessed using a two-sample Student’s *t* test for continuous variables and the chi-square test or Wilcoxon test, when appropriate, for categorical variables. For the SAQ scores, the analysis of covariance (ANCOVA) will be used to compare the change from baseline to 1 year between the QXJYG group and the placebo group [22]. Questionnaire score data, known as nonnormally distributed, will be transformed or analyzed with nonparametric ANCOVA. If appropriate, multivariable linear models will be used to assess the association between independent predictors and the continuous endpoints of the trial. Cumulative event rates of an outcome in the QXJYG and the placebo groups, respectively, will be estimated using the Kaplan-Meier method, and differences between the curves will be tested using the log-rank method. The crude and adjusted hazard ratio and their 95 % confidence intervals will be estimated by the Cox proportional hazards regression model.

The primary outcome will be conducted on the intention-to-treat (ITT) analysis. The ITT set includes all patients randomized to treatment. The per protocol set consists of all patients with no major deviation from the protocol and with an overall treatment adherence rate of 80 % or higher at the end of the study. The safety set consists of ITT patients excluding those who do not take any study medication or who have no record of follow-up after randomization. We will assess the effect that any missing data might have on the results by sensitivity analysis of augmented data sets. Dropouts will be included in the analysis by modern imputation methods for missing data.

We plan to conduct three subgroup analyses: first, we will compare hazard ratios of MACE based upon the level of hs-CRP (below 3 mg/L vs. greater than or equal to 3 mg/L). Second, we will compare the hazard ratios of MACE between SCAD patients with diabetes or not. Finally, we will compare the hazard ratios of MACE between men and women with SCAD.

For all analyses, a value of *P* < 0.05 is considered statistically significant, and all tests are two-tailed. *P* values will be reported to four decimal places. All analyses will be conducted using R software version 2.15.1 (http://www.R-project.org/), unless otherwise noted.

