### Design overview

The rigorous design, organization, and conduct of the trial are supervised by a Steering Committee, which comprises two members from each participating center in addition to the chairman, scientific coordinator and statistician. Eighteen clinical centers in mainland China will participate in the trial, including Xiyuan Hospital of China Academy of Chinese Medical Sciences, China-Japan Friendship Hospital, The First Hospital of Tianjin University of Traditional Chinese Medicine, etc. Data management and statistical analyses will be performed solely by data handlers and data analysts at Beijing Jiaotong University. This study follows the international recommendations for interventional trials [19]. (See the SPIRIT checklist in Additional file 1). All patients must personally sign and date an informed consent document before randomization.

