### Randomization and treatment assignment

Patients are randomized in a 1:1 ratio through a centrally controlled, computer-generated, site-stratified, block randomization schedule. The study granules are labeled with serial numbers, and each patient will be assigned the lowest number available at each participating center. All patients, care providers, attending physicians, laboratory staff and biostatisticians are blind to treatment assignment until the database has been locked. Randomization started on October, 2014. Enrolment of 1500 patients is expected to be completed in August 2016.

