### Sample size

The sample size was calculated based on the expected reduction of incidence in MACE from pre- to post-treatment at 1 year. A previous study suggested that the MACE (death, myocardial infarction, and urgent revascularization) incidence in high-risk patients with SCAD is about 10 % within 1 year [1]. Assuming a MACE incidence reduction to 7 % following treatment with QXJYG added, and given a type I error rate of alpha = 0.05, a power of 80 % (type II error rate of beta = 0.2), the sample size for one arm needed to be 630, resulting in *n* = 2 × 630 = 1260 patients. Considering a dropout rate of 20 %, a total of 1512 patients needed to be allocated to reach the required number of patients for the efficacy analysis. For convenience of randomization, we decided to recruit 1500 patients.

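### Randomisation is blocked within site, but the stated log-rank and Cox comparison does not carry site through; stratifying by centre is a free, minor improvement

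*Protocol article*

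**What the plan says.** The Randomization and treatment assignment section of the protocol article states: "Patients are randomized in a 1:1 ratio through a centrally controlled, computer-generated, site-stratified, block randomization schedule". The Design overview section adds: "Eighteen clinical centers in mainland China will participate in the trial". Site is the only stratification factor named.

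The Statistical approach section estimates event rates by Kaplan-Meier and then says that "differences between the curves will be tested using the log-rank method". It continues: "The crude and adjusted hazard ratio and their 95 % confidence intervals will be estimated by the Cox proportional hazards regression model". On the analysis set it says: "The primary outcome will be conducted on the intention-to-treat (ITT) analysis".

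That section never mentions site or centre. It does not call the log-rank test stratified or unstratified, does not list the covariates of the adjusted model, and does not say which of the log-rank test, the crude hazard ratio and the adjusted hazard ratio is the primary result.

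**The concern.** Blocking within site forces the two arms to be nearly balanced in every centre. Between-centre differences in event rate then contribute almost nothing to the real sampling variation of the treatment comparison. A plain log-rank test does not use this: when centres differ, its variance is somewhat larger than the design warrants, and the hazard ratio from a model without site is a marginal one that lies slightly nearer to 1 than the within-centre ratio. Some variation is plausible, because revascularization is part of the primary outcome and the Discussion places the centres in different geographic areas. The article gives no figure for it.

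At stake are a little power and a clear statement of which comparison counts. The crude hazard ratio is by definition without site. For the test and the adjusted model, the text leaves the matter open.

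**Working it through.** **Inputs from the protocol article.** 18 centres; 1,500 patients, 1:1; one-year event rates of 10% and 7%; 20% dropout; alpha 0.05 ("given a type I error rate of alpha = 0.05") with "all tests are two-tailed".

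**Assumptions, because the article does not give them.** Between-site SD of the log hazard from 0 to 1.0; blocks of 4; exponential event times. The plan has no figure of its own on this point to reproduce.

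**Step 1, effect size.** HR = ln(0.93)/ln(0.90) = 0.0726/0.1054 = 0.689.

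**Step 2, events per stratum.** Mean rate (10% + 7%)/2 = 8.5%. Without dropout, 1,500 × 0.085 = 127.5 events, and 127.5/18 is about 7 per centre.

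**Step 3, what the assumed SDs mean.** The hazard range over the central 95% of centres is exp(2 × 1.96 × SD): about 10-fold at SD 0.6 and about 50-fold at SD 1.0. The upper end of the range is extreme.

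**Step 4, plain against site-stratified log-rank.** 18 equal centres, 20% loss spread uniformly over the year, 4,000 runs per cell. Both tests were applied to the same data, with rejection at |z| > 1.96.

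| Site SD | Type I error, plain / stratified | Power, plain / stratified |
|---|---|---|
| 0 | 5.2% / 5.2% | 51.8% / 51.8% |
| 0.3 | 5.4% / 5.6% | 50.9% / 51.1% |
| 0.5 | 4.7% / 4.7% | 49.6% / 50.5% |
| 0.8 | 4.5% / 5.3% | 48.5% / 50.5% |
| 1.0 | 3.6% / 4.3% | 43.3% / 47.5% |

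The Monte Carlo standard error is √(0.05 × 0.95/4000) = 0.34 points for type I error and about √(0.25/4000) = 0.8 points for power. The comparison to read is the one within a row.

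**Step 5, unequal centres.** The same design with centres of unequal size, exponential dropout of 20% per year and 2,000 runs, at SD 0.3 / 0.6 / 1.0:
- Type I error: plain 4.8 / 4.6 / 4.2%, stratified 5.0 / 5.2 / 5.0%.
- Power: plain 49.1 / 50.3 / 45.0%, stratified 49.1 / 51.5 / 48.4%.

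**Step 6, lower event rate.** The Trial status section reports 30 patients with an event among 1,202 recruited, 906 of them with six months completed, so a rate below 10% is possible. With an assumed 5% control rate, unequal centres and 3,000 runs, power at SD 0.3 / 0.6 / 1.0 is plain 27.7 / 26.4 / 26.8% and stratified 27.7 / 27.1 / 28.7%. The gain is 0 to 2 points.

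**Step 7, the hazard ratio.** Let site multipliers be log-normal with mean 1 (f), and let H be the one-year cumulative hazard (0.1054 control, 0.0726 treated). The marginal cumulative hazard is −ln E[exp(−H f)]. The ratio of treated to control is 0.690, 0.693, 0.698 and 0.704 at SD 0.3, 0.6, 0.8 and 1.0, against a within-site 0.689. The shift toward 1 is at most about 0.015.

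**The case against.** The strongest reply is that silence is not a decision. This is a condensed journal article and the statistical analysis plan is not shown. Log-rank strata and the covariate list of an adjusted Cox model are commonly left to that plan. Site-stratified randomisation and a log-rank method are compatible, so the two sections do not contradict each other. All of this stands. A reader might infer that the analysis ignores the stratification, or that an unstratified log-rank is the declared primary test. The documents support neither: an adjusted hazard ratio is planned and may include site, the log-rank is never called unstratified, and nothing is ranked as primary.

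It is also fair that large between-centre differences are assumed rather than documented, that any error is on the conservative side, and that with about 7 expected events per centre a centre covariate, a frailty term or pooled strata would also be defensible. At modest SDs, conservatism cannot be told from simulation noise.

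What remains is narrower. The one test named for event curves is stated without the one factor used to randomise. Stratifying by that factor cost no power beyond simulation noise in any setting tried, including 18 strata with no heterogeneity at all.

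**Conclusion.** The point holds as a minor one. As stated, the event comparison does not carry site into the test, and whether site enters the adjusted Cox model is open. If centres differ in event rate, the plain log-rank is neutral to slightly conservative. The power given up is nil to about 1 point at a between-site SD of the log hazard up to 0.6, and about 2 to 4 points at 0.8 to 1.0. It is less at a lower event rate. The sizes rest on the assumed SDs, blocks of 4 and exponential event times.

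Two stronger readings should be resisted. A reader might infer that the type I error is compromised; no simulation showed inflation attributable to leaving site out. A reader might also infer that stratifying would rescue the trial's power. It would not: for 10% against 7%, two-sided alpha 0.05 and 80% power, the usual two-proportion formula gives 1,356 per arm against the stated 630, and 750 per arm gives about 55% power before dropout. That shortfall is a separate matter in the Sample size section.

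**What to change.** Before unblinding, state that:
- the primary comparison is a log-rank test stratified by centre;
- the primary hazard ratio comes from a Cox model stratified by centre;
- very small centres are pooled by a rule fixed in advance without knowledge of allocation;
- the unstratified log-rank test and the crude hazard ratio are reported as a sensitivity analysis.

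The covariates of the adjusted Cox model should be named in the same place. If an unseen analysis plan already says this, a cross-reference is enough.

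The cost is a sentence or two in the analysis section. No extra patients, data or visits are needed, and the stated sample size is unaffected.

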Qing-Xin-Jie-Yu Granules (QXJYG) have been used to treat CAD for nearly two decades in mainland China, and previous small-sample studies have demonstrated that QXJYG relieved angina pectoris and decreased cholesterol of patients with CAD [8]. QXJYG consist of five herbal granules, including *Astragalus membranaceus* (Huangqi), *Salvia miltiorrhiza Bunge* (Danshen), *Ligusticum chuanxiong Hort* (Chuanxiong), *Agastache rugosus* (Huoxiang), and *Coptis chinensis* (Huanglian). The pharmacological studies suggested that the bioactive component or structural modification of extracts from Huangqi [9], Danshen [10], and Chuanxiong [11] had effects on cardiac protection, plaque stabilization, inhibition of platelet aggregation, etc., and these three Chinese herbs are also widely used in TCM for treating CAD [12–14]. Moreover, extracts from Danshen and Huanglian exert anti-inflammatory effects [15, 16], and clinical studies showed that they decreased the level of high-sensitivity CRP (hs-CRP) in patients with cardiovascular disease [17, 18].

Therefore, QXJYG is worth investigating in high-risk SCAD patients due to the pleiotropic effect. The assumption is made that QXJYG in addition to conventional treatment may be superior to reduce inflammation of atherosclerosis and finally lead to the reduction of MACE in high-risk SCAD patients. If successful, it will provide an evidence-based complementary therapeutic approach for inhibiting inflammation and reducing MACE from SCAD.

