### Inclusion criteria

The trial will recruit patients of both genders aged 18–75 years with evidence of CAD documented by previous myocardial infarction (>3 months before screening), percutaneous coronary revascularization (>1 month before screening), angiographic or cardiac computed tomography angiographic evidence of ≥50 % stenosis of ≥1 major coronary artery. Also required are two or more of the following four risks: a serum hs-CRP level ≥3 mg/L, a history of hypertension, hyperlipidemia, and diabetes mellitus.

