### Outcomes

The combined primary outcomes include cardiac death, nonfatal myocardial infarction, and revascularization. The combined secondary outcomes include all-cause mortality, re-admission for acute coronary syndrome (ACS), heart failure, malignant supraventricular and ventricular arrhythmia influencing hemodynamics, ischemic stroke, and other thromboembolic events during 1-year follow-up.

Hs-CRP, blood lipids, platelet aggregation rate, echocardiography, electrocardiogram, and Seattle Angina Questionnaire (SAQ) will also be monitored periodically.

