## Discussion

According to our knowledge, this is the first multicenter trial sponsored by the national funding of China to evaluate TCM in combination with conventional treatment on 1-year survival in high-risk SCAD patients.

Atherogenic risk factors including hypertension, hyperlipidemia, and diabetes are common in CAD patients, and clustering of them has a higher age-adjusted, long-term mortality risk [23]. In addition, accumulating evidence has revealed that all these traditional atherogenic risk factors are closely associated with an increased level of CRP, an inflammatory marker with additional prognostic value [24]. A study showed that in SCAD patients, the CRP concentration in the fifth quintile (>3.6 mg/L) showed an about twofold increase in MACE, compared with the first four quintiles [25]. This is in accordance with the consensus view that inflammation has a role in the pathogenesis of cardiovascular events. Therefore, inhibiting chronic inflammation has been regarded a potential strategy to reduce MACE from SCAD.

Chinese herbs have shown multifactorial cardiovascular protective effects, such as lowing plasma lipids [9], reducing oxidative stress [10], and inhibiting platelet aggregation [11], etc. In addition, the anti-inflammatory effects of Chinese herbs have gained much attention recently. Danshen and Huanglian, the two herbs used in QXJYG, also have been demonstrated in many animal or cell culture models to inhibit inflammatory respondence. In ApoE-deficient mice fed with a high cholesterol diet, salvianolic acid B, an extract from Danshen, reduced metalloproteinases-2 (MMP-2) and MMP-9 expression significantly [26]. In human umbilical vein endothelial cells as well as platelets, treatment with extract from Danshen attenuated tumor necrosis factor alpha (TNF-α)-induced expression of CD40. Furthermore, the expression of vascular cell adhesion molecule-1 (VCAM-1) and intercellular adhesion molecule-1 (ICAM-1) as well as the release of soluble VCAM-1, ICAM-1, interleukin-6 (IL-6), IL-8 and monocyte chemoattractant protein 1 (MCP-1) were downregulated [27]. Berberine, an extract from Huanglian, also decreased serum levels of TNF-α and IL-6 in rats with isoproterenol-induced acute myocardial ischemia [28]. This gives a stimulus for large controlled trials to examine the long-term effects of QXJYG in CAD patients, especially those in a high inflammatory state (a serum hs-CRP level ≥3 mg/L, with additional multiple atherogenic risk factors).

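### Effect modification by baseline hs-CRP is examined only through a split at 3 mg/L; adding a continuous interaction term would recover information if the effect changes gradually

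*Protocol article*

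**What the plan says.** The Statistical approach section announces its subgroup work with "We plan to conduct three subgroup analyses: first" and then gives the hs-CRP comparison: "compare hazard ratios of MACE based upon the level of hs-CRP (below 3 mg/L vs. greater than or equal to 3 mg/L". Diabetes and sex follow. Hazard ratios come from a Cox model. I read the hs-CRP level as the baseline value, because this is a subgroup analysis and its cut is the one used at entry.

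Three other places bear on the choice:

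- Inclusion criteria: patients need "two or more of the following four risks: a serum hs-CRP level ≥3 mg/L", or hypertension, hyperlipidemia or diabetes, in any combination of at least two. The subgroup cut is therefore the trial's own entry threshold.
- Background: the treatment is expected to be "superior to reduce inflammation of atherosclerosis and finally lead to the reduction of MACE".
- Discussion: in another cohort of stable patients, "the CRP concentration in the fifth quintile (>3.6 mg/L) showed an about twofold increase in MACE" relative to the lower four fifths. This is the only information on the distribution of CRP.

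The article gives no share of patients at or above 3 mg/L, no assumed shape for the interaction, and no power for this comparison.

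**The concern.** hs-CRP is measured on a continuous scale. Cutting it at 3 mg/L treats 0.3 and 2.9 mg/L as equal, and 2.9 and 3.1 mg/L as opposites. If the benefit grows gradually with inflammation, the two-level comparison uses only part of what the data hold about that gradient.

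Of the three planned subgroups, hs-CRP is the one the article ties to how the treatment is supposed to work. Interaction tests have low power in most trials. An avoidable loss here raises the chance of missing a real gradient.

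**Working it through.** **Plan's own figure.** There is none to reproduce, since the article states no power or event count for this subgroup. The sample size of 630 per arm concerns the main comparison and is not used below.

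**Inputs from the article.** Cut at 3 mg/L and Cox model (Statistical approach); 1:1 allocation (Randomization and treatment assignment); one-year MACE of 10% and 7%, and 1500 patients (Sample size); two-sided 0.05.

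**Inputs assumed.** Log hs-CRP is normal; the log hazard ratio for treatment is linear in it; the share p at or above 3 mg/L lies between 20% and 80%.

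**Step 1: information kept by the split.** Under these assumptions the fraction kept is φ(z)² / [p(1 − p)], where z is the normal quantile at p and φ the normal density.

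- p = 0.50: z = 0, φ = 0.3989, so 0.1592 / 0.25 = 0.637
- p = 0.20: |z| = 0.8416, φ = 0.2800, so 0.0784 / 0.16 = 0.490

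| Share on one side of the cut | Kept | Lost | Events needed relative to continuous (1 / kept) |
|---|---|---|---|
| 50% | 0.637 | 36.3% | 1.57 |
| 40% or 60% | 0.622 | 37.8% | 1.61 |
| 30% or 70% | 0.576 | 42.4% | 1.74 |
| 25% or 75% | 0.539 | 46.1% | 1.86 |
| 20% or 80% | 0.490 | 51.0% | 2.04 |
| 10% or 90% | 0.342 | 65.8% | 2.92 |

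**Step 2: how far this depends on the assumptions.**

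- Uniform marker, median split: 25% lost.
- Effect linear in raw hs-CRP (lognormal, log SD 1): 52% to 90% lost over shares of 20% to 80%.
- True step exactly at 3 mg/L: nothing lost. The fraction in Step 1 is a squared correlation, so in that case the log-linear term is the one that keeps only 49% to 64%.
- Selection by the entry rule. I assumed independent risk factors: hypertension 60%, hyperlipidemia 60%, diabetes 30%, and 20%, 35% or 50% at or above 3 mg/L before selection. The share among eligible patients becomes 30%, 49% or 64%, and the loss 42%, 36% or 38%.

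**Step 3: what it means for power.** Expected events are about 1500 × (0.10 + 0.07)/2 = 127.5. With interaction b per SD of log hs-CRP, the standard error of the continuous term is √(4/127.5) = 0.177. The split multiplies b/SE by the square root of the fraction kept: 0.798 at an even split and 0.700 at 20/80. Power is Φ(b/SE − 1.96).

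For b = 0.4, b/SE = 2.258. The continuous term gives Φ(0.298) = 62%, the even split Φ(1.802 − 1.96) = 44%, and the 20/80 split Φ(1.581 − 1.96) = 35%.

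| b per SD | Continuous | Even split | 20/80 split |
|---|---|---|---|
| 0.2 | 20% | 15% | 12% |
| 0.3 | 39% | 27% | 22% |
| 0.4 | 62% | 44% | 35% |
| 0.5 | 81% | 62% | 51% |

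These powers are approximate: the formula takes events as evenly spread over arms and marker levels. A logistic simulation with 1500 patients gave lower values for −0.4 on the log-odds scale per SD: 51% continuous, 35% even split, 29% with a quarter above. The ordering is the same. With 90 events instead (an assumption), b = 0.4 gives about 47% against 33% and 26%.

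**The case against.** **The cut is legitimate.** It is prespecified, equals the entry threshold, and answers a simple question about patients whom the article itself regards as highly inflamed. A continuous term may also sit in an analysis plan that is not shown. This stands as a reason to keep the split. It does not recover information, and the article does fix how this comparison is to be made.

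**The loss is conditional.** A reader might infer that 36% to 51% is simply thrown away. The documents do not support that, because they give neither the distribution, nor the shape of the interaction, nor the share above the cut. The one hint on shape, the external cohort in the Discussion, contrasts the top fifth with the rest, at a value not far from 3 mg/L. It concerns prognosis and not treatment effect, and it comes from a cohort without this trial's entry rule. It still means a step cannot be excluded.

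**Events are the larger limit.** The interactions for which the continuous term helps most are big. With an average hazard ratio of ln(0.93)/ln(0.90) = 0.69, b = 0.4 in the expected direction implies about 0.69 × e^−0.4 = 0.46 one SD above the mean and 0.69 × e^0.4 = 1.03 one SD below. At b = 0.2 both approaches are weak (20% against 12% to 15%). Trial status reports only 30 MACE among 1202 recruited, 906 of them with six months completed. This stands, and the added term would not make the test well powered.

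**Mechanism.** A reader might also infer that the cut leaves the inflammation hypothesis poorly tested, or that hs-CRP is the lead subgroup. Neither follows. The hypothesis is that treatment lowers inflammation and thereby MACE. Effect modification by baseline hs-CRP is one indirect test of it, and the Outcomes section separately says "Hs-CRP, blood lipids, platelet aggregation rate, echocardiography, electrocardiogram, and Seattle Angina Questionnaire (SAQ) will also be monitored periodically". The subgroup is listed first but not ranked above the others.

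**Baseline values.** The article does not say that every patient has one. The planned split needs the value just as much as a continuous term does.

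**Conclusion.** The point holds as a modest, cheap improvement. As written, the only described test of modification by hs-CRP is a two-level split. Under a normal log hs-CRP, a log-linear interaction and a 20% to 80% share at or above 3 mg/L, that split loses about 36% to 51% of the information. With about 127 events and b = 0.4, power falls from roughly 62% to 35–44%. The loss would be smaller or nil for a step near 3 mg/L, and larger for more uneven splits. It weakens one secondary question and leaves the primary result untouched. The two strata also differ in risk-factor make-up because of the entry rule. That is a separate matter, and a continuous term alone does not remove it.

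**What to change.** In the Statistical approach section, keep the hazard ratios for below 3 and for 3 mg/L or more. Add one Cox model containing treatment, log(baseline hs-CRP) and their product, fitted in patients with a baseline value, and test the product term. Report the hazard ratio with its 95% confidence interval at fixed values, for example 1, 3 and 10 mg/L, and check linearity with a spline. Write this down before unblinding, together with how the split and the continuous result will be read side by side, so that neither is chosen after the fact. The article keeps the biostatisticians blind until database lock, which leaves room for this.

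The cost is a sentence or two of text and one extra model, with no new data. The downside is the log-linear assumption: if the truth is a step, the continuous term is the less efficient test. The retained split and the spline would show this.
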